#### Neuroimaging data analysis

Neuroimaging data processing and statistical analysis were carried out by the individualized Neuroimaging Research Laboratory of Martinos Neuroimaging Center, Massachusetts General Hospital, Harvard Medical School, USA.

The structural MRI data will be analyzed using the VBM toolbox within SPM12. The steps include interlayer time difference correction, spatial difference correction, head motion correction, standardization, and Gaussian smoothing. In the head motion correction process, the images of the subjects whose translation is less than 1 mm and rotation movement is less than 2° will be involved in the follow-up analysis. The fMRI data will be analyzed using the CIVET-pipeline toolbox and SurfStat in MATLAB 2018b. The steps include removing high-frequency components by a bandpass filter, removing the average signal of the whole brain and the signals of the ventricle and white matter, and then registering the data to the surface space of FreeSurfer. T tests and repeated-measures analysis of variance will be conducted to investigate the differences in brain regions in each group. Pearson correlation analysis will be used to test the correlation between fMRI data and clinical variables. According to the results of MRS scanning, the concentration of target metabolites will be statistically analyzed. A paired *t* test will be used to compare within the groups. Analysis of variance and the Wilcoxon rank-sum (if normality is violated) will be used to compare between groups.

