#### Primary outcomes

The primary outcomes include whole-brain structure and function evaluated using fMRI, metabolites in the basal ganglia evaluated using MRS, and cognitive function assessed using the MoCA and CDR.

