### Sample size estimation

The sample size was calculated based on the MoCA scale score as the primary outcome. The sample size was calculated based on the noninferiority comparison of the two groups: *α* = 0.025, 1−*β* = 0.80, *Δ* = − 0.1, which was calculated by PASS software with *n* ≈ 24. Because there was partial shedding in the treatment process, the shedding rate was 20%, and thus, it was appropriate to increase the sample size and take *n* = 30 cases per group. Therefore, 30 cases per group were needed, totaling 90 patients in 3 groups.

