### Statistical analysis

#### Clinical data analysis

Statistical analysis of the clinical outcomes will be performed using SPSS 24.0 statistical software. All statistical tests will be bilateral, and *p* < 0.05 will be considered statistically significant. For clinical information, data will be presented as the mean ± standard deviation. Student’s *t* test and the chi-square test will be used to compare group differences at baseline. A paired *t* test will be used to compare the clinical outcomes within the groups. Analysis of variance and the Wilcoxon rank-sum (if normality is violated) will be used to compare the clinical feature changes between groups. The clinical data, including MoCA, CDR, HbA1c, TC, TGs, HDL-C, and LDL-C, will be converted to domain z scores for correlational analysis with imaging data. Missing data for the primary outcome will be imputed using the multiple imputation method.

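### The repeated-measures ANOVA named for the fMRI primary outcome probably makes it a complete-case comparison, because the only imputation rule does not clearly reach imaging

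*Protocol article*

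**What the plan says.** All places are in the Protocol article.

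- *Primary outcomes*: "The primary outcomes include whole-brain structure and function evaluated using fMRI, metabolites in the basal ganglia evaluated using MRS", with MoCA and CDR alongside.
- *Neuroimaging data analysis*, fMRI test: "T tests and repeated-measures analysis of variance will be conducted to investigate the differences in brain regions in each group". For MRS concentrations the section names a paired t test within groups and ANOVA or Wilcoxon between groups.
- *Neuroimaging data analysis*, motion limit: "the images of the subjects whose translation is less than 1 mm and rotation movement is less than 2° will be involved" in later analysis. The sentence stands among the structural MRI steps, before the fMRI steps begin.
- *Clinical data analysis*, last sentence: "Missing data for the primary outcome will be imputed using the multiple imputation method". That subsection covers clinical outcomes analysed in SPSS.
- *Sample size estimation*: "The sample size was calculated based on the MoCA scale score as the primary outcome"; the required number is one "which was calculated by PASS software with *n* ≈ 24"; and "the shedding rate was 20" per cent, which leads to 30 per group.
- *Withdrawal criteria*, item 4, lists incomplete observation data among the reasons for withdrawing a participant.

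**The concern.** The plan has two routes by which a randomized patient may lack a usable scan: dropout and the motion limit. It then fixes a test that handles such gaps badly. Classical repeated-measures ANOVA discards a patient with one missing or rejected scan, including that patient's good scans. The withdrawal criterion on incomplete data pushes the same way.

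The only remedy stated is imputation, and it sits where its reach to imaging is unclear. *Sample size estimation* uses the phrase primary outcome for MoCA. If the rule stops at clinical data, fMRI has no remedy. If it reaches imaging, it calls for imputing whole-brain maps without saying how.

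Two things are at stake. A complete-case comparison is safe only if loss is unrelated to response, and patients attending 40 sessions who see no early benefit might leave one arm more than the other. The plan also correlates clinical scores with imaging (third aim in *Background*, and both analysis subsections). MoCA imputed for all patients would then stand beside imaging from a smaller, selected subset.

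**Working it through.** **1. The plan's own figure.** Inputs from *Sample size estimation*: 24 evaluable per group and 20% dropout. 24/(1 − 0.20) = 30, which reproduces exactly. Read forwards, 30 × 0.8 = 24, so dropout at the planned rate leaves the number the plan provides for. That number was set for MoCA. No imaging outcome was sized, and no allowance for rejected scans is stated.

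**2. Complete cases after motion rejection.** Assumptions: rejection rate m per scan, independent between scans, with two or three scans per patient. The visit timetable is in a figure not shown. The *Abstract* could mean pre/post only, and *Setting of the study* lists further visits without saying which include MRI. Complete cases per arm = 30 × 0.8 × (1 − m)^k:

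| m (assumed) | k = 2 scans | k = 3 scans |
|---|---|---|
| 0% | 24.0 | 24.0 |
| 5% | 21.7 | 20.6 |
| 10% | 19.4 | 17.5 |
| 15% | 17.3 | 14.7 |

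**3. Bias and precision.** Monte Carlo comparison of complete-case change with a model fitted to all available scans. Assumptions: correlation 0.6 between visits; true effect 0 or 0.6 SD at week 8; 20% dropout in each arm (6 of 30) after week 4; active-arm dropout concentrated in early non-responders; at least 1,000 runs per setting. The strength of selection was varied.

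| Scans | Selection | True effect | Complete-case | All usable scans |
|---|---|---|---|---|
| Three | milder | 0.60 | 0.66–0.68 | 0.60 |
| Three | milder | 0 | +0.06 to +0.07 | 0.00 |
| Three | stronger | 0.60 | 0.70–0.71 | 0.60 |
| Three | stronger | 0 | +0.10 to +0.12 | 0.00–0.02 |
| Two (pre/post) | stronger | 0.60 | 0.71 | 0.66 |
| Two (pre/post) | stronger | 0 | +0.11 | +0.07 |

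With three scans the mixed model removes nearly all the bias, because the week-4 scan carries the information that drives dropout. With two scans it removes 0.05/0.11 = 45% or 0.04/0.11 = 36%.

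The complete-case standard error exceeds that of the all-scans model by:

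- three scans: about 3–4% at m = 0, 4–8% at 5%, 11–13% at 10%, and 16–20% at 15%;
- two scans: about 1% at m = 0, 4% at 10%, and at most 7% at 15%.

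One set of runs treated the covariance as known, which favours the mixed model slightly.

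**4. Scale of the bias.** With correlation 0.6 the variance of a change is 2 × (1 − 0.6) = 0.8 SD². With 24 per arm the standard error of the difference is √(2 × 0.8/24) = 0.26 SD. A bias of 0.06 to 0.10 SD is therefore 0.06/0.26 to 0.10/0.26, or about 0.23 to 0.38 of a standard error.

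**The case against.** The strongest reply is that handling of missing scans usually belongs in the SAP or full protocol, that a condensed article need not give it, and that preferring a mixed model in a self-described pilot is a matter of taste. Silence alone would indeed be no finding. But the article is not silent on method: it names the fMRI test, and that test copes poorly with the losses the plan expects. The better alternative is concrete and costs almost nothing.

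Several stronger readings are tempting, and the document does not support them:

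- **That imaging has no missing-data rule at all.** The imputation sentence refers to the primary outcome, and fMRI and MRS are primary outcomes. Its scope is ambiguous.
- **That the same problem applies to MRS.** Metabolite concentrations are scalars and can be imputed, and repeated-measures ANOVA is not named for them. Their paired t test does drop unpaired patients.
- **That 20% dropout shrinks the sample below plan.** The step from 24 to 30 covers it, and 20% is a planning allowance, not a minimum loss.
- **That the motion limit certainly applies to fMRI.** It is written among the structural MRI steps. The listed steps include slice-timing and head-motion correction, which suit time-series data, so applying it to fMRI is a reasonable inference but no more. Structure is in any case part of the same primary outcome.
- **That the plan declares a complete-case analysis.** It does not. This is the probable result of the classical method; t tests are named beside it.

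It also stands that the bias is well under one standard error, that it needs dropout selective by arm, for which the document offers no evidence, and that a mixed model gains much less if scans are pre/post only.

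**Conclusion.** The point holds in a limited form. As written, the fMRI primary outcome would probably be analysed in patients with complete scans, and the imputation rule does not clearly prevent this. Size of the sample after planned dropout is not the problem. The exposures are selective dropout and motion rejection at an unstated rate.

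Under assumed selective dropout the complete-case bias is about 0.06 to 0.1 SD. A mixed model removes nearly all of it with an intermediate scan, and about half or less with two scans. At 0 to 15% motion rejection the penalty in standard error is about 3 to 20% with three scans and 1 to 7% with two.

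These figures rest on assumptions about scan schedule, rejection rate, between-visit correlation and dropout pattern, none of which the document gives. The direction is firm if dropout follows the assumed pattern; the size is not. The change is worth making because it is cheap, not because serious harm has been shown.

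**What to change.** - In *Neuroimaging data analysis*, replace the repeated-measures ANOVA for fMRI with a linear mixed model using every usable scan from every randomized DCI patient. Terms: arm, visit, arm-by-visit and a patient random effect. Name the end-of-treatment arm-by-visit contrast as the test.
- State that the motion limit applies per scan, so that one rejected image does not remove a patient's others, and say whether it covers fMRI as well as structural images.
- In *Clinical data analysis*, say that multiple imputation applies to MoCA, CDR and, if wanted, the scalar MRS concentrations, but not to whole-brain maps.
- Report unusable scans by arm and reason.

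The cost is analysis wording and slightly more model fitting, with no new data. The mixed model relies on data being missing at random, which is harder to defend if there is no scan between baseline and end of treatment.

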### Quality control

Acupuncture, neurology, and methodology experts reviewed and revised the experimental protocol many times. Before the trial, all staff will attend a series of training sessions. These sessions will ensure that relevant personnel are fully aware of the study protocol and the standard operating procedures for the study. During the trial, supervisors will review case reports and acupuncture procedures twice a month. Throughout the trial, the research team will meet regularly (once every month) to discuss the progress, including recruitment, withdrawal, treatment compliance, and adverse events.

## Discussion

At present, the exact pathogenesis of DCI is still in the exploratory stage. The existing research still lacks imaging markers to accurately explain the cognitive decline of DCI patients, and there are differences in different experimental image processing techniques, such as processing accuracy, brain region segmentation methods, and a lack of ways to analyze the brain imaging data of DCI patients from an individual point of view. The brain imaging data of this study will be completed by the individualized Neuroimaging Research Laboratory of Martinos Neuroimaging Center, Massachusetts General Hospital, Harvard Medical School, USA. This laboratory is the first laboratory in the world to apply rs-fMRI technology to draw the map of functional differences within and between individuals and proposes a new successive recursive method to draw the individual brain network map to improve the reliability of the location results and accurately map the unique functional network organization in each topic [25, 26]. In this way, each patient can be “tailored” to study the cognitive function of his or her brain according to the unique characteristics of his or her brain function, thus helping to make an accurate individualized treatment plan.

In addition, there are no exact and effective drugs or methods for the treatment of DCI in modern medicine, mostly starting from improving symptoms and delaying the disease. On the basis of controlling blood glucose and correcting the disorder of lipid metabolism, drugs to improve the function of brain cells are added for combined treatment, but long-term use easily produces side effects. Related studies have confirmed the important role of acupuncture in the prevention and treatment of diabetes and its complications [13, 27]. However, to date, there have been no properly designed randomized, sham-controlled pilot trials at home or abroad to provide clear evidence to prove the effectiveness of acupuncture in the treatment of DCI and to explain its related mechanism. The intervention method of this study was “Adjust Zang-fu and Arouse Spirit” electroacupuncture therapy, which is based on the previous research results of the research group and the TCM etiology and pathogenesis of DCI. It has the functions of harmonizing Zang-fu organs, freeing *qi* and blood, arousing the brain and regulating spirit. In the early stage, the research group applied this acupuncture method to the clinical treatment of DCI, showing a good clinical effect. At the same time, to eliminate the placebo effect of electroacupuncture, a sham electroacupuncture group was set up, but double-blinding could not be achieved because of the particularity of the electroacupuncture operation.

The main evaluation indicators of this study include brain imaging results and two cognitive assessment scales, and the secondary evaluation indicators include blood glucose and blood lipid detection and four related scales. The time point of evaluation included one evaluation before the treatment period, two evaluations in the treatment period and four evaluations in the follow-up period, for a total of seven evaluations. The brain imaging data of the patients were analyzed at the individual level, and the correlations between the brain imaging, scale results, and test results were analyzed. The purpose of this study was to analyze the changes in brain structure and function in patients with DCI and to explore the therapeutic effect of “Adjust Zang-fu and Arouse Spirit” electroacupuncture on DCI and its correlation with the changes in brain structure and function in patients with DCI.

To summarize, this study is funded by the Project supported by the National Natural Science Foundation of China. The study protocol describes a randomized, sham-controlled pilot trial. The results of this study will provide feasible data and basic information for comprehensively carrying out randomized controlled trial (RCT) experiments of DCI in the future and revealing the mechanism of acupuncture.

## Trial status

This trial is currently ongoing. The study commenced on 10 December 2020 and the anticipated end date of the study is 20 December 2023.

## Data Availability

Not applicable.

## Abbreviations

DCI: Diabetic cognitive impairment
fMRI: Functional magnetic resonance imaging
MRS: Magnetic resonance spectroscopy
MoCA: Montreal Cognitive Assessment Scale
CDR: Clinical Dementia Rating
IADL: Instrumental Activities of Daily Living Scale
HIS: Hachinski Ischemic Scale
SAS: Self-Rating Anxiety Scale
SDS: Self-Rating Depression Scale
DM: Diabetes mellitus
T2DM: Type 2 diabetes mellitus
AD: Alzheimer’s disease
SPIRIT: Standard Protocol Items: Recommendations for Intervention Trials
STRICTA: Standards for Reporting Interventions in Clinical Trials of Acupuncture
HbA1c: Glycosylated hemoglobin A1
TC: Total cholesterol
TGs: Triglycerides
HDL-C: High-density lipoprotein cholesterol
LDL-C: Low-density lipoprotein cholesterol
CRFs: Case report forms
RCT: Randomized controlled trial
